### Potential Benefits and Risks

Conventional focal ablative therapies, RFA and cryoablation, are indicated in patients presenting with an SRM who are poor surgical candidates or who are genetically predisposed to develop multiple tumors. For this study, IRE ablation will be offered to this group of patients in our institution. Early research into renal IRE has proven that the procedural safety and the periprocedural burden are comparable to conventional ablative therapies. The lack of long-term oncological follow-up poses a potential risk as patients cannot be counseled on the risk of residual or recurrent tumor. Post-IRE follow-up will be equal to postcryoablation and post-RFA follow-up and therefore does not carry additional burden with regard to ionizing radiation. When renal function appears to decrease to eGFR below 30 mL/min/1.73 m^2^, only MRI and CEUS will be performed to prevent contrast-induced nephropathy. Furthermore, potential risks associated with IRE ablation for renal tumors using the NanoKnife system are listed in Table 1.

**Table 2 table1:** Potential risks associated with irreversible electroporation of renal tumors.

Potential hazards	Potential effects
Excessive energy delivery	Muscle contraction, burn, damage to critical anatomical structure, unintended tissue ablated, bradycardia/hypotension, vagal stimulation/asystole, electrical shock, myocardial infarction, stroke, death
Insufficient/no energy delivery	Ineffective ablation, no ablation
Unintended mains or patient circuit voltage exposure to patient or user	Electrical shock
Incorrect timing of pulse delivery	Transient arrhythmia, prolonged arrhythmia, stroke, death
Unintended interference with implanted devices containing electronics or metal parts	Myocardial infarction, stroke, death
Unexpected movement of the device and displacement of the electrodes	Hypotension, damage to critical anatomical structure, pneumothorax, mechanical perforation, hemorrhage, unintended tissue ablated, electrical shock, death
Sterile barrier breach	Infection, sepsis

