### Population

A total of 20 patients with solid enhancing SRMs on cross-sectional imaging qualifying for ablative therapy will be enrolled in this study. Eligible patients are 18 years of age and older and will receive a biopsy of the SRM before procedure. All inclusions are reviewed for safety and eligibility by a nephrologist participating in the research project. The inclusion and exclusion criteria for this study are listed in Textbox 1.

Selection criteria. Severe cardiovascular disease is defined as the diagnosis of myocardial infarction, uncontrolled angina, significant ventricular arrhythmias, stroke or severe cardiac failure (New York Heart Association class III and IV) within 6 months prior to inclusion.Inclusion criteria:Age 18 years and olderSolid enhancing SRM on cross-sectional imagingCandidate for ablationSigned informed consentExclusion criteria:Irreversible bleeding disordersInability to stop anticoagulation therapyImplantable cardioverter-defibrillator or pacemakerSevere cardiovascular disease

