### Study Design

This is a prospective, human, in vivo study among 20 patients presenting with solid enhancing SRM on cross-sectional imaging suspect for RCC. Preoperatively, imaging is required through CT, MRI, and CEUS. Furthermore, serum creatinine levels and VAS scores are obtained. A biopsy of the SRM will be performed prior to the ablation. IRE ablation will be performed using CT guidance, and ablation success will be measured directly after the ablation through contrast-enhanced CT. Device-related adverse events will be registered using the CTCAE version 4.0 guideline. At 1 week postablation, only CEUS and MRI will be performed to limit exposure to ionizing radiation. At 3 months, 6 months, and 12 months postablation, CEUS, MRI, and CT will be performed. Additionally at these time points, serum creatinine levels and VAS scores will be obtained, and quality of life will be assessed through Short Form 36 (SF-36) questionnaires. Residual and recurrent disease will be assessed through tissue enhancement on cross-sectional imaging. When imaging appears suspicious for recurrence or residual disease, a percutaneous renal core biopsy will be performed. A study flowchart demonstrating the investigations is outlined in Figure 1.

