#### Irreversible Electroporation Ablation (Study Intervention)

In this study, IRE ablation is performed using the NanoKnife IRE device (AngioDynamics Inc) (Figure 2, A), also registered as the HVP-01 electroporation system. The IRE system contains a low energy direct current generator, a foot switch, and 19G monopolar needle electrodes (15 or 25 cm length). Regulatory authorities have approved both the device and the electrodes through a Conformité Européenne certificate for the use of cell membrane electroporation. Additionally, the US Food and Drug Administration has granted 510(k) clearance with premarket notifications (K060054, K080202, K080376, K080287). Granted 510(k) components are all approved for surgical ablation of soft tissue.

The IRE procedure will be performed at the radiology department CT room with the patient under general anesthesia including deep muscle relaxation to prevent severe muscle contraction [27]. CT imaging will be performed with the patient in the prone or lateral position, dependent on tumor location and position of adjacent organs such as intestines. An interventional radiologist cooperating with a urological surgeon, both experts on percutaneous ablative procedures, will perform the IRE procedure. IRE pulses will be synchronized with ECG under supervision of an anesthesiologist. Prior to ablation, a (second) set of biopsies will be obtained to confirm histopathology. Guided by CT and accompanied by an external spacer for fixation, needle electrodes will be placed (Figure 2, B). The amount of probes and probe placement will be attuned for specific tumor size and location, granting 15 mm between the electrodes with an active tip length of 15 mm. IRE pulses with pulse intensity of 1500 V/cm will be delivered in 90 consecutive pulses of 90 µs *.* Settings are used to disrupt the cell membrane potential in order to achieve irreversible permeability of the cell and subsequent apoptosis. Van den Bos et al demonstrated that with current settings the ablation zone is completely ablated without leaving any skip lesions within the electrode configuration [28].

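### The only implant exclusion covers cardiac devices, although the article's own risk table names interference with electronic implants of any kind

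*Protocol article*

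**What the plan says.** The table under Potential Benefits and Risks sets out hazards of IRE with the NanoKnife system and their possible effects. One row reads "Unintended interference with implanted devices containing electronics or metal parts"; the effects beside it are myocardial infarction, stroke and death. The row does not say which electronic implants are meant.

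Under Population, the article states: "The inclusion and exclusion criteria for this study are listed in Textbox 1". Nothing there marks the list as a selection. The four exclusions are bleeding disorders that cannot be reversed, anticoagulation that cannot be stopped, an ICD or pacemaker, and severe cardiovascular disease. Only the third is about an implant.

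Three general safeguards apply to every patient. The patient must be a candidate for ablation. Under Population, "All inclusions are reviewed for safety and eligibility by a nephrologist participating in the research project". Under Study Design, "Preoperatively, imaging is required through CT, MRI, and CEUS".

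**The concern.** The article identifies electronic implants as a source of risk and also writes an implant exclusion, but the exclusion is narrower than the risk. The hazard row covers electronics in general; the exclusion covers two device types, both cardiac. Someone screening from Textbox 1 would find no exclusion that applies to a patient with, for instance, a neurostimulator (an illustration; the article names no such device). Whether that patient is treated would then depend on someone raising the matter under a general criterion.

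What is at stake is the safety of an individual patient and consistent screening. No estimate or analysis in the trial depends on it.

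**Working it through.** This is a comparison of two texts in the same article; the only arithmetic concerns the cost of the remedy.

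**Step 1. Scope of hazard and exclusion.**

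| Item | Source | Scope |
|---|---|---|
| Hazard | Potential Benefits and Risks, table | Implanted devices with electronics (and with metal parts), no cardiac limit |
| Exclusion | Population, Textbox 1 | ICD or pacemaker |

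For electronic implants, the hazard includes devices that the exclusion does not.

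**Step 2. Does another stated rule cover the difference?**

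- *Severe cardiovascular disease.* The definition is by diagnosis: "Severe cardiovascular disease is defined as the diagnosis of myocardial infarction, uncontrolled angina, significant ventricular arrhythmias, stroke or severe cardiac failure", within 6 months before inclusion. It does not concern devices.
- *ECG synchronization.* "IRE pulses will be synchronized with ECG under supervision of an anesthesiologist". This addresses pulse timing, which has its own row in the risk table.
- *Candidate for ablation.* A general inclusion criterion. It could stop such a patient but does not mention implants.
- *Nephrologist's review.* It covers safety and eligibility for every inclusion, so it too could stop such a patient. The article gives it no implant rule to apply.
- *MRI.* A patient whose implant rules out MRI could not have the required imaging. No MRI contraindication is among the printed criteria, a device that permits MRI would pass, and passing an MRI check does not show that the device tolerates IRE pulses.
- *Operators.* "An interventional radiologist cooperating with a urological surgeon, both experts on percutaneous ablative procedures, will perform the IRE procedure". Their expertise is a further informal check, again without a stated implant rule.

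The first two do not address implants. The other four might catch the patient, but by judgement or by accident of imaging.

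**Step 3. Accrual cost of a wider exclusion.** Inputs from Results: 2 patients included and 1 patient expected every 6 weeks. The target is 20.

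- Remaining accrual: (20 − 2) × 6 = 108 weeks, or 108 / 52 = 2.1 years, in line with the article's estimate of about 2 years.
- One lost candidate: 6 weeks, 6 / 108 = 5.6%.
- Two lost candidates: 12 weeks, 12 / 108 = 11.1%.

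The range of one to two is an assumption, since the article does not say how common other implants are. Zero is also possible, and the cost would then be nil.

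**The case against.** The strongest reply is that a hazard table is not an eligibility list. Other rows that list death, such as excessive energy delivery or electrode displacement, have no matching exclusion. The effects listed for the implant row are mainly cardiovascular, so the excluded cardiac devices may be the main concern. Each patient must also be a candidate for ablation, pass a safety review and have an MRI, and the full protocol, which is not shown, may say more.

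Much of this stands, and it rules out three stronger readings that a reader might infer.

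- *That a patient with another electronic implant is simply eligible.* The general safeguards could each hold that patient back. The supportable statement is that no stated exclusion applies.
- *That the article attributes death to non-cardiac implants.* The row pools all implants and gives one list of effects. It does not say which effect belongs to which kind of device.
- *That a rule for metal implants is missing.* The article gives no type or location of metal implant, and a procedural check of that sort may be left to the full protocol. Its absence from a condensed article shows nothing.

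The reply does not remove the mismatch for electronic implants. Energy delivery and electrode displacement are features of the procedure, whereas an implant is a patient characteristic that can be known at screening, and the article already handles it by exclusion. The point is that an exclusion which is printed, in a list presented as the study's criteria, is narrower than a hazard which is also printed. If only cardiac devices were meant, the hazard row should say so.

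**Conclusion.** The point holds as a minor patient-safety matter and a cheap improvement. The stated implant exclusion is narrower than the hazard the article names, and the difference is left to safeguards that do not mention implants. It is a wording gap, not an error that invalidates the design.

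Its size cannot be expressed as a risk, because the article gives neither the frequency of other electronic implants among ablation candidates nor a rate of interference. The patients concerned are few in kind: those with a non-cardiac active implant that permits MRI, who are judged candidates for ablation and pass the nephrologist's review. In a cohort of 20 there may be none.

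The conclusion rests on reading Textbox 1 as the study's criteria, as the article presents it. If the full protocol already has a wider criterion, only the article's wording needs to be brought into line.

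**What to change.** Replace the exclusion for ICD or pacemaker with: any active implanted electronic device, including ICD and pacemaker. No other criterion needs to change, and no new test or visit is needed.

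The downside is that an occasional candidate may be lost, at about 6 weeks of accrual each. The patients affected may have few alternatives, since the article offers IRE to poor surgical candidates and to those genetically prone to multiple tumors. If the sponsor has evidence that certain non-cardiac devices are safe under IRE, the alternative is to limit the hazard row accordingly, so that hazard and exclusion match.

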### Data Safety Monitoring Board

The study will be monitored by a data safety monitoring board (DSMB) consisting of an independent urologist and a clinical epidemiologist. This team will monitor patient safety and treatment efficacy data during the study. Monitoring procedures are predetermined and described in the DSMB charter, approved by the institutional review board (IRB) of the Academic Medical Center University Hospital in Amsterdam. Additional DSMB meetings can be called at any time if deemed necessary by the DSMB or the principal investigator.

### Analysis

The NanoKnife console produces 2-dimensional images including a prediction of the ablation zone, which is perpendicular to the needle. The AMIRA (FEI) software package system will bundle the 2-dimensional ablation zone cross-sections around the length of the exposed tip. This will estimate the following:

Ablation zone volume (cm^3^)3-Dimensional reconstructionAblation zone shape/symmetry

An experienced uroradiologist will evaluate CT and MRI images for the following characteristics *:*

Volume of ablation zone (cm^3^)Shape of ablation zoneResidual tumor on ablation zone borderSkip lesions or signs of recurrence within ablation zoneTransition zone between ablated and normal renal tissueDamage to adjacent vital structures

For MRI and CT, whole-mount kidney and ablation zone will be calculated. The AMIRA software system will be used to obtain a 3-dimensional kidney and ablation zone. CEUS will be performed by an interventional radiologist and will be used for 2-dimensional imaging only.

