## Methods

### Study Objectives

To determine the clinical efficacy of IRE ablation for SRMs (≤4 cm) assessed by the recurrence and residual disease rate at follow‐up using cross‐sectional imagingTo evaluate the use of computed tomography (CT), magnetic resonance imaging (MRI), and contrast-enhanced ultrasound (CEUS) in the visualization of (non)complete ablation to assess the radiological extent of the ablation zone at 1 week, 3 months, 6 months, 9 months and 1 year after IRETo evaluate perioperative outcomes after IRE ablation of SRMs (≤4 cm) such as (1) renal function, measured by creatinine levels and estimated glomerular filtration rate (eGFR), (2) average length of hospital stay, (3) quality of life, and (4) postoperative pain score after IRE, measured by a visual analog scale (VAS) and analgesics useTo determine the safety and feasibility of IRE ablation of SRMs (≤4 cm) by evaluating device and procedural adverse events using Common Terminology Criteria for Adverse Events (CTCAE) version 4.0

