#### Computed Tomography Imaging (Standard)

As provided per ablation protocol, CT imaging will take place during the diagnostic phase and during the procedure. According to our ablation surveillance protocol, follow-up CT imaging will be performed at 3 months, 6 months, 1 year, 1.5 year, 2 years, 2.5 years, and 3 years after IRE ablation. After this, patients will be followed up yearly up to 10 years. This is the standardized follow‐up after ablative therapy at our institution (see Figure 1). Patients with an eGFR below 60 mL/min/1.73 m^2^ will undergo pre- and posthydration in order to prevent contrast-induced nephropathy. Patients with an eGFR below 30 mL/min/1.73 m^2^ are excluded from CT imaging.

CT imaging will be performed in a supine position in a dual source CT system, SOMATOM Force (Siemens Medical Solutions), or in a Sensation 64-slice CT scanner (Siemens Medical Solutions). First, a survey scan from the upper border of the diaphragm to the ischium bone will be made. Next, noncontrast series in the same section will be performed. Subsequently, 120 mL of Ultravist-300 diluted with NaCl 0.9% will be administered intravenously with a speed of 4 mL/s. Following contrast injection, arterial, venous, and delayed series will be obtained after 45 seconds, 115 seconds, and 600 seconds, respectively. Source images will be recontructed in coronal and sagittal planes using multiplanar reconstruction in the venous and delayed series.

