### Sample Size

Our sample size was deliberated on the basis of previous similar study designs that used comparable sample sizes of 6 to 20 patients [20,23-25]. In this phase of research (phase 2B IDEAL Collaboration), a small cohort of N=20 was chosen to acquire first results in order to progress to a large trial. A sample size of 20 patients does not permit reliable comparative statistical analysis. In this study, IRE is intended as a curative therapy. Consequently, there will be no exploration in number of probes and configuration settings. Hence, analysis will be restricted to averages and standard deviations of assessed radiologic features.

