For the follow-up of renal masses, the most frequently used imaging modality is contrast-enhanced CT. Multiple studies have demonstrated that MRI and CEUS are adequate imaging techniques for follow-up after IRE [36-40]. However, the use of contrast-enhanced CT scan in the follow-up after kidney ablation might be precluded because of potential nephrotoxicity or ionizing radiation exposure in young patients. In the population of patients that receive ablation for their renal mass comorbidity, older age and decrease in renal function are common since their presence entails a clear indication for ablative therapy. Furthermore MRI, applicable to a broader range of the ablated population, may not be easy available and may increase costs. Hence, in this population it is vital to investigate whether other imaging modalities will detect recurrences and residual disease in renal masses with the same accuracy as CT and MRI.

Nononcological outcomes of IRE have been minimally investigated in renal tumors. A total of 2 small studies described serum creatinine levels and demonstrated no significant changes in renal function or transient increase of creatinine which resolved after 1 month [23,24]. Postprocedural pain and length of stay is described by Thomson et al in liver, kidney, and lung (N=36, kidney tumors n=4). While 4 patients were admitted longer than 24 hours, none of these patients had kidney tumors. Postprocedural pain was registered through analgesics use, demonstrating 2 patients who required intravenous or intramuscular analgesics. No patient required prolonged analgesic use after discharge. Quality of life has not been reported in current IRE literature. Insight in nononcological outcomes, including quality of life, is urgently required since treatment decision making is often influenced by this. Particularly in the ablation population, meaning elderly patients with multiple comorbidities, quality of life after an intervention is of great importance.

Categorized as a level 2b study according to the IDEAL classification, this study will provide prospective information on kidney IRE ablation with an extensive description on the radiological evolution of the ablated lesion along time as well as mid-term oncological outcomes. Lastly, we will provide prospective data on quality of life, kidney function, pain level, and duration of admittance after IRE.

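### No residual-disease reading is specified for CEUS, and averages with standard deviations cannot show whether CT, MRI and CEUS agree in the same patient

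*Protocol article*

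**What the plan says.** All places are in the protocol article.

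- **Study Objectives.** The second objective is to evaluate the use of CT, MRI and CEUS "in the visualization of (non)complete ablation" over follow-up.
- **Analysis.** "An experienced uroradiologist will evaluate CT and MRI images for the following characteristics", followed by six items. Two of them bear directly on incomplete ablation: residual tumour at the edge of the zone, and skip lesions or recurrence inside it. No list is given for CEUS, only this: "CEUS will be performed by an interventional radiologist and will be used for 2-dimensional imaging only".
- **Sample Size.** After stating that 20 patients are too few for reliable comparison, the section concludes: "Hence, analysis will be restricted to averages and standard deviations of assessed radiologic features".
- **Study Design.** "Residual and recurrent disease will be assessed through tissue enhancement on cross-sectional imaging". No modality is named there. A core biopsy follows when imaging is suspicious.
- **Computed Tomography Imaging (Standard).** Patients with eGFR below 30 mL/min/1.73 m² "are excluded from CT imaging". Potential Benefits and Risks repeats this for patients whose renal function falls to that level.
- **Discussion, Conclusions.** The authors consider it vital to learn "whether other imaging modalities will detect recurrences and residual disease in renal masses with the same accuracy as CT and MRI".

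**The concern.** The objective names three modalities, but the items that would identify incomplete ablation are assigned to two. CEUS is a study intervention, done at baseline and at four visits after treatment. If its findings on residual enhancement are not recorded in a fixed form at the scan, they may be hard to recover later.

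The stated analysis adds a second gap. Residual tumour and skip lesions are yes/no findings, for which an average and SD are a poor summary. For continuous features such as ablation-zone volume, similar averages on two modalities do not show that the modalities agree in individual patients. A reader who wants to know whether one modality could stand in for another would not find the answer in the planned output.

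**Working it through.** The plan has no calculated figure to reproduce. N=20 was chosen by precedent (earlier studies of 6 to 20 patients), without an error rate, effect size or SD.

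**1. Objective against reading list**

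| | CT | MRI | CEUS |
|---|---|---|---|
| Named in the second objective | yes | yes | yes |
| Scans after treatment | directly after; 3, 6, 12 months | 1 week; 3, 6, 12 months | 1 week; 3, 6, 12 months |
| Residual tumour and skip lesions/recurrence listed as reading items | yes | yes | not specified |
| Three-dimensional reconstruction | yes | yes | no |

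**2. Yes/no findings.** Assume for illustration that each of two modalities is positive in 2 of 20 patients (the documents give no rate). Both then have mean 0.10 and SD √(0.1 × 0.9) = 0.30. The SD follows from the mean and adds nothing. Chance agreement is 0.1 × 0.1 + 0.9 × 0.9 = 0.82, and kappa = (observed − 0.82)/(1 − 0.82).

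- No shared positives: 0 + 16 = 16/20 agree (80%); kappa = −0.02/0.18 = −0.11
- One shared: 1 + 17 = 18/20 agree (90%); kappa = 0.08/0.18 = 0.44
- Both shared: 2 + 18 = 20/20 agree (100%); kappa = 1.00

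The planned summary is identical in all three cases.

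**3. Continuous features.** With equal means and equal SDs on two modalities and between-modality correlation r, the 95% limits of agreement are ±1.96 × SD × √(2(1 − r)). The values of r are assumptions.

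- r = 0.5: ±1.96 SD
- r = 0.7: ±1.52 SD
- r = 0.9: ±0.88 SD

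Again, the means and SDs do not distinguish these cases.

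**4. Different patients behind the averages.** Anyone below the eGFR threshold contributes MRI and CEUS but not CT. Averages taken by modality could therefore rest on different patients. The documents give no expected count, so the size of this effect is unknown.

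**5. What a paired description would deliver.** Exact 95% intervals for agreement with all 20 pairs available:

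- 20/20: 83.2% to 100%
- 19/20: 75.1% to 99.9%
- 18/20: 68.3% to 98.8%

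Each limit of agreement would have a standard error of about √(3/20) = 0.39 times the SD of the within-patient differences.

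**6. Why not accuracy.** Biopsy follows only suspicious imaging, so imaging-negative patients are not verified. Precision is a further obstacle: at an assumed 10% failure rate, 20 × 0.10 = 2 events are expected. If both are detected, the exact 95% interval for sensitivity is 15.8% to 100% (lower bound √0.025 = 0.158).

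**The case against.** The strongest defence is that the trial never promised a comparison. The objective is to evaluate the use of the modalities, the Sample Size section openly gives up reliable comparative analysis, and the same-accuracy sentence is rationale in the Discussion, not an endpoint. This stands against any claim that the whole objective fails: description of CT and MRI is achievable as planned. It does not dispose of the point, because cross-tabulating paired findings is itself description and needs no power.

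A second defence concerns CEUS. The sentence limiting it to two dimensions follows the text on three-dimensional reconstruction, so it most naturally means that no CEUS volume will be computed. Study Design does not restrict which modality shows enhancement, and the CEUS section says the schedule serves to assess lesion size and characteristics. A reader might infer that CEUS will not be read for residual disease; the documents do not say so. They only fail to specify such a reading where they specify it for CT and MRI.

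Third, the restriction to averages and SDs does not say that they are taken per modality, and the mean and SD of within-patient differences would fit the wording. That is fair for volumes. It does not help with yes/no items, and no within-patient difference is mentioned.

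A reader might also infer that one unmasked radiologist reads both CT and MRI, which would bias their agreement upward. The article is silent on masking, reading order and number of readers. An article may leave these to the full protocol, so no finding rests on them.

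**Conclusion.** The point holds in limited form. The list of reading items covers two of the three modalities in the objective, and the stated analysis suits neither yes/no findings nor within-patient comparison. The same planned summaries are compatible with kappa from -0.11 to 1.00, and with limits of agreement from ±1.96 SD to ±0.88 SD. These ranges rest on an assumed 2/20 positives per modality and assumed correlations of 0.5 to 0.9; they illustrate the gap and do not predict results.

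It would go too far to say that the imaging objective cannot be answered. What the stated plan does not secure is the CEUS part and any statement on agreement between modalities. An accuracy statement would lack support even after the fix, because verification by biopsy is partial. The article itself discloses the absence of histological confirmation after treatment as a limitation.

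**What to change.** 1. **Analysis section.** Have the radiologist who performs CEUS record, at each scheduled scan, the same yes/no items in CEUS terms (enhancement at the border of the zone, enhancement within it), plus in-plane diameters.
2. **Sample Size section.** Replace the restriction to averages and SDs with a descriptive paired analysis by patient and time point, using only patients with both images of a pair. CEUS–MRI pairs are scheduled at 1 week and at 3, 6 and 12 months; pairs with CT at 3, 6 and 12 months. For yes/no items, give 2×2 tables with agreement and exact 95% intervals. For CT–MRI volume and for CEUS diameter in a matched plane, give within-patient differences with limits of agreement. Report the number of pairs each time.
3. **Wording.** Call the result descriptive agreement, not accuracy, and give the reason: imaging-negative patients are not verified.

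This needs no extra scan, patient or reader. It costs slightly longer CEUS reporting and a few more tables, and the intervals will be wide. Only 2 patients had been included when the article was written, so an early change would cover nearly the whole cohort. If the sponsor prefers not to record CEUS findings in this way, the alternative is to restrict the objective to description and to drop the implied comparison for CEUS.
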